## Abstract

**Background:**

Microvascular angina (MVA) is characterized by anginal chest pain, an abnormal stress test, and normal coronary arteries on coronary angiography. Although the exact pathogenesis remains unclear, endothelial dysfunction is a contributing factor. To date, there exists no specific therapy for this disease. Phosphodiesterase-5 inhibitor improves the endothelial function and subsequently microvascular circulation. The aim of this study is to identify whether udenafil offers benefits in the treatment of MVA in female patients, who have a perfusion defect in their cardiac magnetic resonance image (CMR), but normal coronary arteries.

**Methods/Design:**

The ‘Understanding of Chest Pain in Microvascular Disease Proved by Cardiac Magnetic Resonance Image: (UMPIRE)’ trial is a multicenter, prospective, randomized, placebo controlled trial, designed to evaluate the effect of udenafil on myocardial ischemia and symptoms in female patients with MVA. The myocardial ischemia will be quantified by myocardial stress perfusion defect in CMR. A total of 80 patients with proven perfusion defect in adenosine-stress CMR will be randomly assigned to either the udenafil treatment group (daily dose of 100 mg) or the placebo group for three months. The primary endpoint is >25% improvement in perfusion defect size in adenosine-stress CMR from baseline. The secondary endpoints include <25% improvement in perfusion defect size, chest pain frequency, ST depression in stress test, Duke score in stress test, quality of life (QoL) assessment by SF-36 questionnaire, sexual dysfunction assessment by BISF-W (Brief Index of Sexual Functioning for Women) self-assessment questionnaire, and biomarkers for endothelial function.

**Discussion:**

The UMPIRE trial is the first randomized controlled trial to evaluate the efficacy of udenafil in female MVA patients. If udenafil demonstrates cardioprotective effects, it may provide a novel therapeutic option to reduce myocardial ischemia and improve cardiac function in female MVA patients.

**Trial registration:**

Clinical Trials.gov: NCT01769482 (registered on 20 November 2012).

## Background

Microvascular angina (MVA), also known as cardiac syndrome X, is characterized by anginal chest pain, an abnormal stress test indicative of myocardial ischemia, and normal coronary arteries on angiography. The condition is not as benign as originally reported. While patients with stable MVA have an excellent prognosis [1], unstable MVA patients presenting with acute coronary syndrome have an increased risk of death or myocardial infarction [2]. Women are more affected than men. The current therapeutic options for MVA are limited.

An impairment of endothelium-dependent vasodilation due to reduced nitric oxide (NO) release mainly accounts for the proposed mechanisms of MVA [3]. NO availability plays a critical role in the regulation of microvascular endothelial functions and the arterial structure [4–6]. Many of the biological actions of NO are mediated by 3’5’-guanosine monophosphate (cGMP), which is rapidly degraded by cGMP phosphodiesterase (PDE). Recently, phosphodiesterase-5-inhibitor (PDEi) has been reported to improve the endothelial function in animal and clinical studies [7–10]. PDE inhibitors improve cardiac performance in patients with heart failure [11] and reduce infarct size and attenuate cardiac dysfunction after ischemia/reperfusion injury or permanent coronary artery occlusion [12]. While short-term cardiovascular effects of PDE inhibitors have been studied, the effects of chronic PDEi administration are not well known, especially in women with MVA.

In the ‘Understanding of Chest Pain in Microvascular Disease Proved by Cardiac Magnetic Resonance Image: (UMPIRE)’ study, we tested whether udenafil offers benefits in the treatment of female MVA patients who have a documented perfusion defect in CMR.

## Methods/Design

### Overview

This trial will be a multicenter, prospective, randomized, double-blind, placebo controlled trial to demonstrate the superiority of the therapeutic benefit of low-dose udenafil over a placebo in the treatment of female MVA patients. The working hypothesis is ‘udenafil improves vascular function and, consequently, alleviates ischemia in women with MVA who have a confirmed perfusion defect in CMR and normal coronary arteries on coronary CT angiography (CCTA) or coronary angiography’.The protocol of the trial has been registered with Clinicaltrials.gov (registration number: NCT 01769482) and a brief flowchart of the whole study is summarized in Figure 1.

**Figure 1 Fig1:**
[figure not shown]
**Study flowchart.** CAG; coronary angiography, CTCA; coronary CT angiography, CMR*;* Cardiac magnetic resonance image.

### Endpoints

The primary endpoint is a >25% improvement from baseline in perfusion defect size in adenosine-stress CMR after three months of udenafil treatment. The secondary endpoints include a <25% improvement in perfusion defect size, chest pain, quality of life, and sexual functions after three months of udenafil treatment. Detailed endpoints are listed in Table 1.

**Table 1 Tab1:** **Endpoints**

	Endpoint details
Primary endpoint	>25% improvement in perfusion defect size in adenosine-stress CMR from baseline to three months after udenafil treatment
Secondary endpoints	<25% improvement in perfusion defect size in adenosine-stress CMR from baseline to three months after udenafil treatment
	Decrement of frequency of chest pain
	Improvement of ST-depression in stress test
	Improvement of Duke score in stress test
	Improvement of QoL assessment by SF-36 questionnaire
	Improvement of sexual dysfunction assessment by BISF-W self-questionnaire
	Improvement of biomarkers for endothelial function

CMR*;* Cardiac magnetic resonance image, QoL; Quality of life.

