#### Statistical analysis

For comparison between the udenafil treatment and the control group, we would use student’s t-test for continuous variables and χ^2^-test for categorical variables. To evaluate improvement of perfusion defect size >25% between udenafil treatment and control group, we would analyze using Fisher’s exact test. The difference in the continuous outcome between the experimental and control group will be assessed using generalized linear models. Frequency differences will be tested using χ^2^-test or Fisher’s exact test. We will be analyzing this data using an intention-to-treat analysis. All randomized patients will be included in the analysis. A *P* value of less than 0.05 will be considered statistically significant.

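### The first secondary endpoint, less than 25% improvement in defect size, has no lower bound: read literally it is nearly the primary in reverse, and read as partial improvement it has no direction of benefit

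*Protocol article*

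**What the plan says.** Table 1 of the protocol article gives the primary endpoint as ">25% improvement in perfusion defect size in adenosine-stress CMR from baseline to three months after udenafil treatment". The first secondary endpoint in the same table is "<25% improvement in perfusion defect size in adenosine-stress CMR from baseline to three months after udenafil treatment". Measure, modality and interval are identical, and only the inequality sign differs.

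The wording is not confined to the table. The Endpoints section has "The secondary endpoints include a <25% improvement in perfusion defect size", and the Methods/Design part of the abstract has "The secondary endpoints include <25% improvement in perfusion defect size". None of the three places sets a floor such as more than 0%, and none describes the endpoint as partial response or as a continuous change. The remaining secondary endpoints in Table 1 are all phrased as a favourable change (an improvement or a decrement). This is the only one defined by falling below a threshold.

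For the primary, the Statistical analysis section states "To evaluate improvement of perfusion defect size >25% between udenafil treatment and control group, we would analyze using Fisher’s exact test". For other categorical comparisons it states "Frequency differences will be tested using χ^2^-test or Fisher’s exact test". It specifies intention to treat with all randomized patients included.

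**The concern.** An endpoint defined as falling below a threshold, without a floor, is met by a patient who improves a little, by one who does not change and by one who gets worse. Almost everyone who fails the primary therefore succeeds on this secondary. Comparing the arms on it largely repeats the primary comparison with the labels exchanged.

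The risk lies in interpretation. A drug that works as planned would show a lower rate than placebo on its first-listed secondary endpoint. A drug that does nothing would show a high rate in both arms, under a label containing the word improvement. As defined, the only other endpoint on the trial's main imaging measure says nothing beyond the primary about smaller degrees of response.

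**Working it through.** **1. Is the primary a binary responder endpoint?** The Sample size calculation section uses a formula for a categorical variable, two tails, alpha 0.05, 80% power and 10% dropout, and arrives at 38 per arm (76 in total). It mentions 25% for udenafil and 2% for control but does not call the 25% a proportion of patients. Treating both as responder proportions, with the pooled-variance formula and no continuity correction:

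n = [z₀.₉₇₅·√(2p̄(1−p̄)) + z₀.₈₀·√(p₁(1−p₁) + p₂(1−p₂))]² / (p₁−p₂)², where p̄ = (0.25 + 0.02)/2 = 0.135.

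- First term: 1.960 × √(2 × 0.135 × 0.865) = 0.947
- Second term: 0.842 × √(0.1875 + 0.0196) = 0.383
- n = (0.947 + 0.383)² / 0.23² = 33.4, rounded up to 34 per arm
- With dropout: 34/0.9 = 37.8, rounded up to 38 per arm, 76 in total

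This matches the stated figure exactly. The proportions are an inference from that match.

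**2. Literal reading.** With no floor, every patient with a known change other than exactly 25% is in one endpoint or the other.

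- Expected rate on the secondary, udenafil: 1 − 0.25 = 75%
- Expected rate on the secondary, placebo: 1 − 0.02 = 98%
- Difference: 23 percentage points, with placebo higher

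At the planned 40 per arm, the nearest whole numbers of responders are 10/40 and 1/40 (0.02 × 40 = 0.8):

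| Endpoint | Udenafil | Placebo | Odds ratio | Fisher p |
|---|---|---|---|---|
| Primary (above 25%) | 10/40 | 1/40 | (10×39)/(30×1) = 13.0 | 0.0069 |
| Secondary (below 25%) | 30/40 | 39/40 | (30×1)/(10×39) = 0.077 = 1/13 | 0.0069 |

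The equality is general when the two endpoints partition the patients. Over all 41 × 41 = 1,681 possible tables at 40 per arm, the largest difference between the two Fisher p-values is about 3 × 10⁻¹⁶, which is rounding error.

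**3. When the partition is not exact.** Suppose, as an illustration, that 10% of each arm (4 of 40) meets neither endpoint because the three-month scan is missing or the change is exactly 25%. If responders stay at 10 and 1, the secondary becomes 40 − 10 − 4 = 26 of 40 against 40 − 1 − 4 = 35 of 40. Fisher p is then 0.034, while the primary stays at 0.0069. The p-values now differ, but the direction still favours placebo.

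**4. Partial-improvement reading (above 0 and below 25%).** Relative to placebo, let an effective drug move m patients from this band up into the primary responders, and k patients from no improvement into the band. The band count changes by k − m. At the planning rates there are 10 − 1 = 9 extra responders. If all 9 come from the band and k = 0, the count falls by 9. If none comes from the band and k > 0, it rises. Either sign is compatible with benefit, so neither a higher nor a lower count can be interpreted on its own.

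**5. The boundary.** Both inequalities are strict, so a change of exactly 25% belongs to neither endpoint. If defect size is the summed integer segment score described under Visual analysis, such changes can occur (4 to 3, or 8 to 6). The article does not say that defect size is that score.

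**The case against.** The strongest reply is that in ordinary usage a worsened or unchanged defect is not an improvement of any size. The other secondary endpoints name favourable changes, so the authors probably meant partial improvement. On that reading the endpoint is not the complement of the primary, and the 75% and 98% figures do not apply. This is a fair account of the likely intent. But no floor is written in any of the three places, and step 4 shows that the partial-improvement reading leaves the endpoint without a direction of benefit.

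A reader might also infer that the secondary test must always return the primary's p-value. The documents do not support that. It requires that nobody is at exactly 25%, that no three-month scan is missing and that Fisher's test is used for both. The plan expects 10% dropout, the article does not say how a missing scan is classified, and a chi-square test is allowed for frequencies.

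Nor does it follow that partial response goes unmeasured. CMR is scheduled at screening and at week 12, so the data will exist, and generalized linear models are planned for continuous outcomes, although defect size is not named among them.

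Finally, the article is a condensation, and a fuller document may hold an operational definition. That would excuse missing detail. Here a definition is stated, three times, and it does not work as stated.

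**Conclusion.** The point holds, at moderate severity. As written, the first secondary endpoint is either nearly the reverse of the primary (literal reading) or a middle band whose count has no defined favourable direction (partial-improvement reading). Under neither reading can it support a conclusion about udenafil beyond what the primary already gives.

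Under the literal reading the size is about 75% of udenafil and 98% of placebo patients meeting the endpoint. This rests on taking 25% and 2% as responder proportions, which is inferred from reproducing 38 per arm, and on leaving aside patients at exactly 25% or without a scan.

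It would be wrong to infer that the main result is compromised. The primary endpoint, its test and the sample size do not depend on this secondary.

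**What to change.** In Table 1, the Endpoints text and the abstract, replace this endpoint with one of the following:

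- the change in perfusion defect size from baseline to three months, compared between arms with adjustment for the baseline value; or
- an ordered outcome with three levels (worse or unchanged; improved by more than 0 and up to 25%; improved by more than 25%), compared by a Wilcoxon or proportional-odds test.

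In either case, state that exactly 25% counts as the middle level, which leaves the primary at above 25% as it stands. Either option has a clear direction of benefit and uses the smaller changes that the primary discards.

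The cost is a change of wording and a registry update. Both scans are already scheduled, so no new data are needed. The article reports that recruitment is still under way, so the change can be made before unblinding.

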### Patient population

Patients who are at least 18 years of age, have chest pain and positive adenosine-stress CMR, and normal coronary artery on CCTA or coronary angiography will be included in this study. A positive adenosine-stress CMR is defined as a perfusion defect of >25% of transmurality. Two high-volume centers in the Republic of Korea will participate and enroll eligible patients. The following patients are excluded from the study: patients with contraindication to MR contrast media or MR imaging, any heart rhythm other than sinus rhythm, congestive heart failure, chronic kidney disease, contraindication to PDEi, or uncontrolled diabetes mellitus. The detailed inclusion and exclusion criteria are summarized in Table 2.

**Table 2 Tab2:** **Inclusion and exclusion criteria**

**Inclusion criteria**	
1	MVA patients with typical symptom and positive adenosine-stress CMR and with normal coronary artery in CCTA or coronary angiography.
2	Definition of positive adenosine-stress CMR: perfusion defect >25% of transmurality (by two radiologists based on visual assessment and qualitative assessment in core-lab)
3	Gender: female
4	Age: 18 to 80-years-old
**Exclusion criteria**	
1	Patient has a contraindication to CMR contrast media or CMR imaging
2	LVEF <50%
3	Any heart rhythm abnormality other than sinus rhythm
4	Valvular heart disease with more than moderate degree
5	Renal failure
6	Congestive heart failure
7	Myocardial infraction
8	Myocarditis
9	Congenital heart disease
10	Pericarditis
11	Variant angina (positive provocation test with ergonovine or acetylcholine)
12	GERD (conformed by esophagogastroduodenoscopy)
13	Pregnant women, suspected pregnant women or lactating women
14	QT prolongation syndrome or taking drugs that prolong the QT interval:
	- Antiarrhythmics class IA; quinidine, procainamide
	- Antiarrhythmics class III; amiodarone, sotalol
15	Pre-analytical within 30 days of screening in a clinical trial that may affect the influence of udenafil:
	- Other PDE-5 inhibitors (for example sildenafil, tadalafil)
	- Nitrates/NO donor (for example nitroglycerin, isosorbide mononitrate, isosorbide dinitrate, amyl nitrate/nitrite, sodium nitroprusside, and nicorandil)
16	Pre-analytical within seven days of screening in a clinical trial that may affect the metabolism of udenafil:
	- Antibacterials (for example erythromycin)
	- Antifungals (for example itraconazole, ketoconazole)
	- Antivirals (for example ritonavir, saquinavir, amprenavir, indinavir, nelfinavir)
	- Cimetidine
	- Grapefruit juice
17	Allergy or sensitivity with PDE-5 inhibitors

CCTA; Coronary CT angiography, CMR; Cardiac magnetic resonance image, GERD; Gastroesophageal reflux disorder, LVEF; Left ventricular ejection fraction, MVA; Microvascular angina, NO; Nitric oxide, PDE-5; Phosphodiesterase-5.

If all of the inclusion criteria are met and none of the exclusion criteria apply, the patient will be required to provide written informed consent, as required by the institutional review board (Samsung Medical Center Institutional Review Board, Seoul National University Bundang Hospital Institutional Review Board) in accordance with the Declaration of Helsinki.

### Randomization and interventions

After the patients are enrolled in the study, the patients will be randomized to the udenafil treatment group or the placebo group by a web-based computerized program which will be independently managed at T&W software (Three and Water software, Seoul, Republic of Korea). The flowchart of the study design is shown in Figure 1.

### Udenafil treatment protocol

After random assignment, patients in the udenafil treatment group will receive 100 mg udenafil daily (Dong-A Pharmaceutical, Seoul, Republic of Korea) for three months. Since headache and facial flushing are common side effects of udenafil, the dose of study medication will be reduced by 50% if severe headache develops. In patients with serious side effects the study medication will be stopped.

### Cardiac magnetic resonance imaging (CMR)

#### CMR imaging

##### Cine imaging

All CMR studies will be performed using a 1.5 T MRI scanner (Siemens Avanto, Erlangen, Germany or Intera CV release 10; Philips Medical Systems, Best, Netherlands) with a phased array cardiac coil. Hemodynamic parameters, oxygen saturation, and lead vector ECG (Electrocardiogram) rhythm will be continuously monitored throughout the whole CMR exam. Following image localizers, ventricular long and short axis cine images will be acquired in end expiration with retrospectively ECG-gated steady-state free precession sequences (image matrix 128 × 128, read field of view (FOV) 340 mm, phase FOV 75 to 100% of the FOV read, echo time 1.12 ms, flip angle 70°) with slice thickness 8 mm and intersection gaps of 12 to 15 mm. The adenosine-stress CMR protocol is illustrated schematically in Figure 2.

**Figure 2 Fig2:**
[figure not shown]
**Adenosine-stress CMR protocol.** Following image localizers, ventricular long cine images will be acquired. Adenosine (140 mcg/kg/min) will be infused for 6 minutes before stress perfusion imaging at the time of gadolinium injection. Early gadolinium imaging will be followed by short axis cine and then rest perfusion imaging. Late gadolinium enhancement images to evaluate the scar and patient viability will conclude the scan. Study duration will typically be 35 to 40 minutes.

##### Adenosine infusion protocol

Adenosine (Adenoscan™, Sanofi-Synthelabo, Berlin, Germany) will be infused at 140 μg/kg/min [13], via a 20-gauge cannula sited in an antecubital vein, using a syringe pump (Graseby™ 3500; Graseby Medical LTD, Watford, Hertfordshire, UK). Adenosine will be infused for a minimum of 6 minutes before acquiring stress images. Indications for terminating adenosine infusion are persistent or symptomatic third degree atrioventricular block, severe hypotension (systolic blood pressure <90 mmHg), or bronchospasm. Scans will be supervised by an MRI trained clinician with access to immediate resuscitation facilities.

##### Perfusion imaging

Patients will undergo pharmacological stress and rest perfusion. In 1.5 T scanners (Siemens Avanto, Erlangen, Germany or Intera CV release 10; Philips Medical Systems, Best, Netherlands), a breath-hold MR first-pass perfusion examination will be performed. Electrocardiographic gating and triggering will be performed using the vector cardiographic method. Fast survey images will be acquired to determine the true short axis of the left ventricle. After the acquisition of rest cine scans in the standard views, adenosine will be infused at a dose of 140 μg/kg/min for up to 6 minutes [13]. During the adenosine infusion, electrocardiographic activity will be continuously monitored, and blood pressure and heart rate measurements will be obtained every minute. Within the last minute of infusion, the adenosine stress MR perfusion scan will be performed to visualize the three short-axis slices of 8 mm section thickness using 40 dynamic acquisitions. During the inspiratory phase of the second breath, a bolus of gadodiamide (Omniscan; GE healthcare, Pittsburgh, PA**,** United States) will be injected using a power injector (Spectris; Medrad, Indianola, Pennsylvania) into an antecubital vein at a dose of 0.1 mmol per kilogram of body weight and an injection rate of 4 ml/s, followed by a 20 mL saline flush. Stress perfusion MR images will be obtained with a gradient-echo sequence by using saturation recovery steady-state free precession (SR-SSFP). After 15 to 25 minutes, identical MR perfusion scan at rest will be continued to allow adequate clearance of the first bolus of the contrast agent.

#### CMR analysis

##### Visual analysis

Visual analysis of myocardial perfusion will be performed offline by consensus of two CMR specialists. Rest and stress perfusion images of the three short axis sections (base, mid, and apex) will be viewed side by side. The first-pass study will be analyzed both in qualitative and semi-quantitative ways, with a 16-segment left ventricle model. On qualitative assessment, perfusion defects are defined as subendocardial or transmural visually dark myocardial areas, respecting coronary distribution, with a delay of at least 2 seconds compared with remote healthy myocardium, and persisting for at least 10 frames [13]. A score will be assigned for each left ventricular segment according to the following scale: 0 = no perfusion defect; 1 = subendocardial perfusion defect with transmural extension <25%; 2 = subendocardial perfusion defect with transmural extension between >25% and 50%; 3 = subendocardial perfusion defect with transmural extension between >50% and 75%; and 4 = subendocardial perfusion defect with transmural extension >75%. For each patient a total score will be obtained as the sum of the individual scores of each segment. If a perfusion defect is also present at rest, the stress-related (ischemic) score will be calculated as the difference between the score after stress minus the score at rest. All cases will undergo evaluation for late gadolinium enhancement. A normal scan requires the absence of both reversible ischemia and late gadolinium enhancement. A representative example of a patient with inducible ischemia is shown in Figure 3.

